## Abstract

**Background:**

Due to the prevalence and associated adverse health consequences of negative body image among adolescents globally, there is a need to develop acceptable, effective, and scalable interventions. School-based body image interventions delivered by trained teachers show promise in reducing negative body image in adolescents. However, there is currently a lack of evidenced-based body image interventions for use in low- and middle-income countries (LMICs). This paper outlines a protocol for the development and evaluation of *Dove Confident Me Indonesia: Single Session*, a single-session, teacher-led body image intervention for Indonesian adolescents.

**Method:**

The effectiveness of the intervention will be evaluated using a cluster randomised controlled trial design. Due to the COVID-19 pandemic, the trial will be conducted online. Trained teachers or school guidance counsellors will deliver the intervention. Self-report questionnaires will be collected at three time points: baseline, post-intervention, and two-month follow-up. The primary outcome is body esteem. Secondary outcomes are internalisation of appearance ideals, mood, engagement in life activities, tendency to engage in appearance comparisons, and skin shade satisfaction. A minimum of 1000 participants will provide 95% power to detect small-to-medium intervention effects. To account for attrition and potential internet issues, the sample will comprise of 2000 Indonesian adolescents in grades 7–9, attending state junior high schools in Surabaya, East Java. Quantitative and qualitative data on acceptability of the intervention will also be collected from teachers and students. Additionally, fidelity of lesson implementation will be assessed. This project received ethical approval from the Universitas Indonesia and the University of the West of England. The intervention will be disseminated in junior high schools throughout Indonesia via UNICEF’s Life Skills Education (LSE) programme, which will be freely available for teachers to download.

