Progression criteria based on (i) recruitment, (ii) participant retention, (iii) adherence to intervention, and (iv) lesson fidelity will be used to ascertain how we proceed from the pilot to the main trial. In addition, though adverse effects of the intervention or research trial are not expected based on findings from similar previous intervention studies (e.g., [36, 37, 49]), the research team will screen the data for safety (e.g., trends indicating declining body esteem). Criteria will be rated for each parameter with a traffic light system from red (stop, major issue for the progress of the trial) through to amber (amend and proceed with caution) through to green (continue, no issues threatening the success of the trial) [55]. The progression criteria are presented in Table 3.

**Table 3 Tab3:** Progression Criteria from Pragmatic Pilot to Main Trial

Criteria		Green	Amber	Red
Recruitment	How many parents consent and corresponding students assent (target *n* = 120)	**50% or above** Continue with main trial	**30 and 49%** Consult research team to advise on changes to recruitment plan	**Below 30%** The pilot study may need to be extended
Participant Retainment	Student completion up until T2 in both arms	**70% or above** Continue with main trial	**50–69%** Consult research team to advise on changes to survey administration protocol	**Below 50%** The main trial will need to reconsider how surveys are administered
Intervention Adherence	Number of students attending online lesson for the full duration (supplemented with qualitative feedback on online delivery of lesson)	**90% or above** Continue with main trial	**70–89%** Consult research team to advise on changes to lesson delivery	**Below 70%** The main trial will need to reconsider how lesson is delivered
Fidelity of Lesson Delivery	Percentage of the lesson covered by teacher, assessed by two fidelity checkers	**90% or above** Continue with main trial	**60–89%** Consult research team on possible changes to lesson intervention or training	**Below 60%** Fully reconsider lesson intervention/training

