### Sample size calculation

A meta-analysis of 50 RCTs evaluating single-session adolescent psychological health interventions [41] reported a mean effect size of Hedges *g* = 0.32, which can be interpreted as a small-to-medium effect size (small effect size = 0.2; medium effect size = 0.5). This is consistent with findings from the RCT evaluation of *Dove Confident Me: Single Session* [36], which reported standardised effects ranging from small to small-to-medium for outcome measures. Based on a more conservative, lower bound of d = 0.2, a sample size of *n* = 500 girls and *n* = 500 boys per arm would provide in excess of 95% power over any positive range of correlation between baseline and outcome data at T2 and would have in excess of 90% power for separate analyses for girls and boys. We will oversample to mitigate the effects of loss to follow-up due to student absence or technical difficulties to increase population coverage and external validity. Therefore, the target study sample size will be approximately 2000 adolescents: 1000 (500 girls, 500 boys) in the control condition, 1000 (500 girls, 500 boys) in the intervention condition. It is estimated that 20 eligible schools will be recruited to achieve this sample size.

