### Strengths

A core strength of this project is the participatory approach adopted by the multi-stakeholder project team, which has led to careful, culturally-sensitive co-creation of the intervention and provides opportunity for widespread dissemination across the country. Embedded within UNICEF Indonesia’s LSE curriculum, *Dove Confident Me Indonesia: Single Session * is projected to reach hundreds of thousands of adolescents attending state-run junior high schools by the end of 2022. This meets calls for intervention research to centre implementation planning at the core of development and design from both within the field of body image [66] and mental health practice more broadly [47]. By embedding our intervention within an established, acceptable framework and dissemination modality (i.e., UNICEF Indonesia’s LSE) we are ensuring the programme is set up for widespread dissemination and implementation. Importantly, as the dissemination plan has already been arranged with project stakeholders, namely UNICEF and the Dove Self-Esteem Project, a due-diligence contingency plan to remove the body image lesson from the current version of UNICEF Indonesia’s LSE programme has been arranged should the results from this trial indicate the programme has unintended negative effects on adolescent well-being upon full analysis. However, given that this intervention is based on an existing evidence-based intervention and has been carefully co-created by international and local experts, teachers, and school children, we are confident it will have the hypothesised positive effects on adolescents’ well-being.

Relatedly, we have task-shifted the delivery of the intervention to community providers (i.e., teachers and school guidance counsellors). Again, this a crucial strategy in enhancing wide-scale dissemination and ensuring intervention sustainability in contrast to relying on highly trained specialist providers [67–69]. Additional strengths of this study design are the use of a cluster RCT design and the large sample size. The cluster RCT design helps circumvent contamination of the control group [52] and the targeted 2000 participants will ensure adequate power to this study, while accounting for potential participant drop-out at follow-up time points.

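### The abstract and the sample size section give different required sample sizes, and the by-gender power claim of more than 90% carries no allowance for loss to follow-up

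*Protocol article*

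**What the plan says.** The abstract (Method) gives a minimum and an enlarged figure. The minimum: "A minimum of 1000 participants will provide 95% power to detect small-to-medium intervention effects". The enlargement: "To account for attrition and potential internet issues, the sample will comprise of 2000 Indonesian adolescents".

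The Sample size calculation section cites a mean effect of g = 0.32 from a meta-analysis, "which can be interpreted as a small-to-medium effect size (small effect size = 0.2; medium effect size = 0.5"). It then sizes the trial on something smaller: "Based on a more conservative, lower bound of d = 0.2". At that effect it takes 500 girls and 500 boys per arm. It claims more than 95% power at T2 for any positive baseline correlation, and more than 90% for girls and boys analysed separately. It continues: "We will oversample to mitigate the effects of loss to follow-up due to student absence or technical difficulties". The conclusion drawn from this is that "the target study sample size will be approximately 2000 adolescents: 1000 (500 girls, 500 boys) in the control condition", with the same numbers in the intervention condition. No retention rate or inflation factor is given.

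The Strengths section repeats the allowance: "the targeted 2000 participants will ensure adequate power to this study, while accounting for potential participant drop-out at follow-up time points".

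The only retention figures in the article are the pilot progression criteria (Table 3), where the measure is "Student completion up until T2 in both arms" and 70% or above is rated green.

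**The concern.** The number of students who must supply T2 data is 1000 in one place. In the other, the power claims are computed on 2000. The section that announces oversampling ends on the number it started from, so the stated allowance is 2000/2000 = 1.00, or none.

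This matters most for the analyses split by gender, which the Data analysis section prespecifies at T2 and T3. Their power claim is attached to 500 per gender per arm, which is exactly the number to be recruited. A reader cannot tell how many students must be analysed, how much loss the plan can absorb, or which comparisons stay adequately powered after that loss.

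**Working it through.** **Inputs.** From the Sample size calculation: d = 0.2 (SD = 1), 1000 per arm overall, 500 per gender per arm, 20 schools. From the abstract: 1000 in total, taken as 500 per arm. From Table 3: 70% retention to T2, used only as an illustration. Assumed, because the article does not state them: two-sided 5% test and 1:1 analysis. Clustering is left out until step 5.

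**Formula.** λ = d / √[(1 − r²) · 2/n], with n per arm and r the correlation between baseline and T2 score. Power ≈ Φ(λ − 1.96). An exact t calculation differs by at most about 0.001 in the cases below.

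**1. The overall claim in the sample size section.**
- n = 1000, r = 0: λ = 0.2/√0.002 = 4.47, power 0.994. Any r above 0 raises it, so the claim of more than 95% reproduces.
- n = 700 (30% loss): λ = 3.74, power 0.962 to 0.963.
- n = 650: λ = 3.61, power 0.95. The overall comparison can therefore lose 1 − 650/1000 = 35% before falling to 95%.

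**2. The by-gender claim.** The claim is more than 90% with 500 per gender per arm.
- Full retention, r = 0: λ = 0.2/√0.004 = 3.16, power 0.885.
- For 90%, λ must reach 1.96 + 1.28 = 3.24, so √(1 − r²) = 3.162/3.2415 = 0.9755 and r = 0.22 (about 0.23 with the t distribution).

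After loss to T2:

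| Loss | Per gender per arm | Power, r = 0 | Power, r = 0.5 |
|---|---|---|---|
| 0% | 500 | 0.885 | 0.955 |
| 10% | 450 | 0.851 | 0.934 |
| 20% | 400 | 0.807 | 0.904 |
| 30% | 350 | 0.75 | 0.86 |

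At 350, λ at r = 0 is 2.646. Reaching 3.2415 needs √(1 − r²) = 0.816, so r is about 0.58; at r = 0.6 power is 0.91.

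**3. The abstract's sentence.** For 500 per arm:
- d = 0.2: 0.885 at r = 0, and 0.95 only from r of about 0.48.
- d = 0.228, r = 0: 0.95.
- d = 0.32, r = 0: λ = 5.06, power 0.999.

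Neither of the article's candidate effect sizes gives 95% at r = 0. The sentence states neither an effect size nor a correlation that would.

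**4. The enlargement.** The abstract implies 2000/1000 = 2.0, an allowance for 50% loss. The sample size section implies 2000/2000 = 1.0, an allowance for 0%.

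**5. Clustering, for orientation only.** The article gives no intraclass correlation. With 20 schools of about 100, the design effect is 1 + 99 × ICC. An assumed ICC of 0.01 gives 1.99, an effective 1000/1.99 ≈ 503 per arm and overall power of 0.887 at r = 0 (0.955 at r = 0.5). An assumed 0.02 gives 2.98, about 336 per arm, and 0.736 (0.849 at r = 0.5). The slack in step 1 is therefore an upper limit.

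**The case against.** The strongest reply is that little is actually wrong. The main power claim is correct, with room for substantial loss, so on an individual-level calculation the Strengths statement holds for the overall comparison. That stands. A reader might infer from the identical 2000 figures that the trial as a whole has no attrition margin; the arithmetic does not support that. The missing margin concerns the by-gender claim.

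It can also be said that the abstract speaks of small-to-medium effects, a label the sample size section attaches to 0.32 and not to 0.2. A reader might infer that the abstract's 95% is an arithmetic error. The article does not establish that: at 0.32 the power is well above 95%, and at 0.228 it is exactly 95%. The fault is a sentence that cannot be tied to the stated design effect and names no other.

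One might go further and apply the by-gender claim to the abstract's 1000, that is 250 per gender per arm. The article makes that claim only for 500, so the comparison would be unfair.

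Finally, 70% is a pilot progression threshold and not the main trial's planned retention. That is correct. The 30% loss row is a scenario, chosen because it is the lowest retention the pilot would rate green. The planned baseline adjustment also helps, and at r = 0.5 the by-gender power survives a 20% loss (0.904). But the article ties its by-gender figure to no particular correlation or retention, so it cannot rely on a favourable pair.

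**Conclusion.** The point holds as an inconsistency in the required sample size and an unsupported by-gender power figure. The requirement is 1000 in the abstract, while the sample size section computes its power on 2000, and the oversampled target equals that calculated number.

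The overall claim of more than 95% at d = 0.2 is right before clustering. The by-gender claim of more than 90% is slightly short at r = 0 with nobody lost (0.885). After appreciable loss it holds only with a substantial baseline correlation: about 0.49 or more at 20% loss (the r = 0.5 entry in the table is just above 0.90) and about 0.58 at 30%.

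These figures rest on a two-sided 5% test, which the article does not state, and on independent observations, which a trial randomising schools will not have. Allowing for clustering can only lower them if the intraclass correlation is positive. The contradiction between the sections depends on none of these assumptions.

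**What to change.** Keep 2000 as the number recruited. In the abstract, the Sample size calculation and the Strengths section, give the same three figures, each with its effect size: students needed with T2 data, assumed retention, and students recruited.

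Restate the by-gender power for the number expected to be analysed, at a stated baseline correlation and retention, or withdraw the claim of more than 90%. Either name the effect size behind the abstract's 1000 and 95%, with power recomputed to match, or delete that sentence. The restated power should reflect randomisation by school, with the assumed intraclass correlation given.

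This changes text only and needs no extra enrolment. The cost is that the stated power, especially by gender, becomes less favourable.

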**Discussion:**

This paper presents *Dove Confident Me Indonesia: Single Session,* a culturally adapted school-based intervention designed to improve Indonesian adolescents’ body image. It details the plan for evaluation, highlighting the strengths and limitations of the proposed study design. It will be informative for others aiming to adapt evidence-based school curricula to promote well-being among adolescents in LMICs.

**Trial registration:**

NCT04665557. Registered 11th December 2020.

**Supplementary Information:**

The online version contains supplementary material available at 10.1186/s12889-021-11770-0.

## Background

Negative body image, often conceptualised as body dissatisfaction or low body esteem, is a prevalent concern among adolescents with far-reaching physical and mental health implications [1, 2]. Adolescents are particularly vulnerable to experiencing negative body image due to the physical, cognitive, emotional, and social changes characteristic of this developmental stage [3–5]. Studies indicate that as many as two-thirds of early- to mid-adolescents in high-income countries report negative body image [6–8]. This is concerning as longitudinal evidence indicates that negative body image during adolescence predicts poor outcomes including low self-esteem, depression, disordered eating, and the onset of risky health behaviours, such as smoking [7, 9, 10].

Negative body image among adolescents is not limited to those living in high-income and/or English-speaking countries. Al Sabbah and colleagues [11] found comparable rates of negative body image among adolescents in high-, middle-, and low-income countries. Further, data from cross-cultural studies show adolescents living in Asian countries including China, Japan, Korea, and Malaysia report similar or worse body dissatisfaction than those in regions such as Australia, Europe, the UK, or the US [12–15]. However, there is a current lack of adequately powered, theory-driven body image intervention research in low- and middle-income countries (LMICs) [16, 17]. This underscores the need for transparent intervention development and evaluation research focused on alleviating negative body image among adolescents in these settings.

### Indonesian context

Indonesia is an upper-middle-income, majority Muslim country in Southeast Asia and is the world’s fourth most populous nation [18]. Nascent studies indicate body image is an important health issue for Indonesian adolescents [19–22]. For instance, consistent with research on body image among adolescents in other Asian countries and in high-income, English-speaking countries, Azizah and Kristiutami [19] found 58.7% of Indonesian adolescents aged 14–19 (76.2% girls) in the city of Tangerang (a large urban centre in Greater Jakarta, Banten province) reported negative body image. Further, these studies present cross-sectional evidence that negative body image is correlated with disordered eating behaviours among Indonesian adolescent girls [21, 22] as well as low self-acceptance [20]. In addition, a recent U-Report poll^1^ [23] completed by over 3000 adolescents in Indonesia (53% girls) from all 34 provinces found 77% wanted to change something about their appearance. According to the same poll, just under half (47%) reported that worrying about how they look held them back from engaging in important life activities, and 89% expressed that they would like to learn ways to improve their body image.

Macro-level factors, including rapid urbanisation and modernisation, the globalisation of media and advertising, social media, and a legacy of colonisation have all been positioned as contributing to negative body image in LMICs, including Indonesia [24–27]. Consistent with global gendered appearance ideals, research indicates the thin ideal is dominant and often internalised by women in affluent, urban regions of Indonesia [28]. Meanwhile, Prianti notes that for men, the athletic body ideal is widely promoted in Indonesian media, in line with “westernized notions of masculinity” ([24], p116).

Beyond the influence of Eurocentric appearance standards, a Pan-Asian ideal, characterised by a blend of European and Asian features, is becoming dominant across Asia [29]. The Pan-Asian ideal places particular emphasis on the face and an “Asian White” skin shade ([29], p74). It can be attributed, in part, to the popularity of Japanese and Korean popular culture and a booming skin-lightening industry in Asian markets, including Indonesia [29, 30]. For instance, Korean pop culture (including K-pop and K-beauty) is recognised as an important influence on body image, particularly for younger generations in Indonesia and notably promotes a homogeneous appearance ideal emphasising an extremely thin body type and very light skin [31, 32]. Taken together, there is a clear need for evidence-based body image interventions in Indonesia to help young people resist unrealistic appearance ideals and bolster their overall body esteem.

### School-based body image interventions

Schools are an ideal environment to deliver universal, cost-effective body image interventions [16, 33]. Existing school-based interventions have found positive results in improving body image among adolescents in high-income, English-speaking countries, such as Australia and the UK (e.g., *Media Smart* [34]; *Me, You & Us* [35]; *Dove Confident Me: Single Session* [36] and *Dove Confident Me: Five Session* [37]). Further, evidence suggests that task-shifting programme delivery from highly trained subject experts (e.g., psychologists or body image researchers) to trained teachers and school staff is feasible and effective, thus promoting cost savings, increased reach, and sustainability [35–37]. Given the insufficent number of trained mental health providers coupled with the stigma associated with mental health conditions in LMICs including Indonesia [38, 39], universal, school-based interventions with teacher-led delivery stand to be a more acceptable and sustainable way to provide mental health-related education to adolescents [40].

### Single-session interventions

Single-session interventions are defined as the intentional delivery of a single-encounter intervention [41]. A growing body of evidence supports the capacity of single-session interventions to provide significant short-term improvements in youth psychopathology [41, 42], and more specifically, reduce negative body image among adolescents [16, 43]. On average, single-session body image/eating disorder prevention interventions are less effective than multi-session interventions [44, 45]. However, their value lies in their potential for greater accessibility and opportunities for dissemination at scale [41]. Particularly in LMICs, attention to the mental health of students is often not considered within the school curriculum [39, 46], thus bringing into question the feasibility and acceptability of running multi-session programmes. Single-session interventions may provide a more realistic intervention option for schools to provide mental health-related education among adolescents [40, 47]. Consequently, a single-session intervention stands to be a good first step in introducing body image curriculum in Indonesian schools.

### Dove Confident Me

In line with evidence highlighting the prevalence and adverse consequences of negative body image among young people in Indonesia and reports that Indonesian adolescents would like to learn ways to improve their body image, the development and evaluation of a body image intervention for adolescents in Indonesia is timely. Recognising this, a partnership has been initiated among body image and education experts, health professionals, UNICEF Indonesia, and the Dove Self-Esteem Project (DSEP; a social purpose industry initiative) to develop, evaluate, and disseminate a single-session body image intervention for delivery by schoolteachers in Indonesia. This intervention will be embedded within UNICEF Indonesia’s new Life Skills Education (LSE) curriculum, a government-approved programme for junior high schools, which will be disseminated to schoolteachers in Indonesia via online training in collaboration with the Indonesian government’s Ministry of Education and Culture. It will be freely available to all state junior high schools across Indonesia via a government website.

The *Dove Confident Me: Single Session* school-based intervention initially evaluated in the UK [36] served as the conceptual base for the development of the present single-session body image intervention in Indonesia, *Dove Confident Me Indonesia: Single Session*. In this first evaluation, Diedrichs and colleagues [36] found the intervention led to immediate improvements in British adolescents’ body esteem, mood, life engagement, as well as a reduction in disordered eating behaviours. Notably, results from the evaluation of * Dove Confident Me: Single Session* in the UK found more favourable outcomes when the teachers delivered the lesson compared to external researchers [36]. Moreover, the extended five-session version of *Dove Confident Me*, first evaluated in UK schools similarly yielding positive outcomes [37], has recently undergone cultural adaptation for use in urban Indian schools [48]. A recent randomised controlled trial (RCT) evaluating *Dove Confident Me India* [49] found both immediate and sustained improvements in body esteem, highlighting the potential for adapting *Dove Confident Me* across cultural contexts. In addition, findings from this research show that with cultural adaptation, *Dove Confident Me* can be an acceptable intervention in Asian contexts for both teachers and students [48], and therefore was chosen as the basis for the present intervention.

*Dove Confident Me Indonesia: Single Session* is a 90-min body image lesson designed to be delivered to mixed-gendered school classes of adolescents aged 12–15 years, facilitated by teachers or school guidance counsellors. *Dove Confident Me Indonesia: Single Session* integrates two evidence-based and theoretically grounded techniques to attenuate negative body image: media literacy and cognitive dissonance. Media literacy techniques include critical thinking and enhancing ‘realism scepticism’ to (1) increase recognition that digitally altered images are unrealistic and thus inappropriate targets for appearance comparisons and (2) draw attention to the underlying motives for advertisers to curate and edit images depicting appearance ideals in order to sell products [50]. Cognitive dissonance techniques aim to reduce individuals’ internalisation of societal appearance standards and subsequently improve body image by encouraging adolescents to actively challenge these ideals via verbal, written, and behavioural exercises [45]. Accordingly, *Dove Confident Me Indonesia: Single Session* has three learning objectives: (1) Identify the ways that media images can be altered to conform to and perpetuate unrealistic appearance ideals; (2) identify the negative consequences of unrealistic appearance ideals on themselves, their friends, and community; and (3) identify strategies to help themselves and others resist unrealistic appearance pressures.

